#### **S. 3.3.2. Sampling**

Male smokers, who met the inclusion criteria for the study in Shenzhen will be invited to participate. The inclusion criteria are: the participants should be (1) male resident aged 18 or above; (2) smoking at least one cigarette per day averagely during the past 1 months (exhaled CO verified); (3) get married and partner has been pregnant (no deformity); (4) able to communicate in Mandarin (including reading Chinese); and (5) have a smartphone for intervention and follow-up. Smokers who meet the above criteria but are currently involved in other smoking cessation programs or the pilot study and/or mentally or physically unfit for communication will be excluded.

Based on previous study conducted in Mainland China, the 6-month quit rate for the control group was approximately 14.8%[60, 61]. According to previous RCT of text message intervention, the rate ratio of quit rate for the intervention and control group was 2.18 (intervention group: 10.7%, control

group: 4.9 %)[62]. To detect a significant difference of quit rate between intervention and control groups with a power of 80 and 5 % significance level, 264 subjects per group will be needed. Assuming an retention rate of 80% at the 6-month follow-up, the total sample size taking into account in the recruitment session and attrition is 990.

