#### **S. 3.3.7. Data collection procedures**

Male smokers will be recruited in the Obstetrics and Gynecology clinics at tertiary public hospitals in China when the males accompany with their partners to have a body check. Invitation letter will be sent to the public hospitals to participate in this study. After obtain the permission of these hospitals. These eligible people were invited to participate in the study after telling the purpose of this study. They will be given the option of participating or refusing and will be told that their participation is voluntary without prejudice. Written consent will be obtained from those subjects accepting to receive the interventions.

After the consent is obtained, the participant will be coded. By using a computer random selection procedure from the code, the participants will be randomly allocated into three arms, which are intervention group 1, intervention group 2 and control group. The subjects' demographic information, smoking characteristics, self-efficacy level, and exhaled carbon monoxide (CO) level at the baseline will be assessed by the research nurses. The biochemical validation will be done by a staff member who has not delivered the intervention and conducted the telephone counselling follow-up. Yet all subjects will not be blinded, because they will receive the behavioral intervention.

In the intervention group, the smokers will receive an intervention including video, brief advice, and pamphlet. In the intervention group 2, the subjects will text message, brief advice and pamphlet. For the participants in the control group, they will only receive a brief advice and pamphlet materials at the baseline. The detail procedure of data collection is presented in the figure 2 below.

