#### **S. 3.4. Data analysis**

The IBM SPSS Statistics (SPSS: Version 20.0; SPSS Inc., Chicago, IL, USA) for windows will be used for data analysis. A p-value  $<0.05$  was considered as statistically significant. Descriptive statistics will be used to calculate the frequency and percentage (categorical data) or the mean and standard deviations (continuous data) of different demographic and social-economic characteristics. The intention-to-treat (ITT) principle will be used for outcome comparison between groups. Information missed at follow-up will be considered as non-quitters, non-reducers or do not use the video if no records about watching full video set. Multiple imputation will be used to fill the missing value of the demographic information at baseline. One-way ANOVA test or Mann-Whitney test and chi-square test will be used to compare the differences of nicotine dependency, stage of readiness to quit, and self-efficacy among three groups between baseline and 6-month follow-up for those who continued smoking. Logistic multiple regression will be conducted to examine the association between the intervention and the outcomes at 6-month follow-up. Subgroup analysis will be

performed by the first time to be father, level of nicotine dependence, and readiness to quit at baseline.

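### The 264 per group given for 80% power matches a one-sided 5% test of 4.9% against 10.7%; the conventional two-sided test needs 335, and the cited 14.8% control rate is not used

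*Protocol*

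**What the plan says.** Protocol S. 3.3.2 (Sampling) offers two sets of planning figures. The first is from Mainland China, where "the 6-month quit rate for the control group was approximately 14.8" per cent. The second is a text-message trial in which "the rate ratio of quit rate for the intervention and control group was 2.18"; the rates in brackets are 10.7% for intervention and 4.9% for control. The conclusion is that "with a power of 80 and 5 % significance level, 264 subjects per group will be needed". With 80% retention at 6 months the total becomes 990. The paragraph does not say which control rate was used, whether the 5% is one- or two-sided, or which of the three arms are contrasted.

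S. 3.3.7 says that "the participants will be randomly allocated into three arms". S. 3.4 (Data analysis) says that a p-value below 0.05 "was considered as statistically significant", and that "Logistic multiple regression will be conducted to examine the association between the intervention and the outcomes at 6-month follow-up". It also applies intention to treat and counts anyone missing at follow-up as a non-quitter. The words one-sided and two-sided appear in neither section.

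**The concern.** A reader who recalculates with the usual two-sided test and the only pair of rates given does not arrive at 264. The same reader finds a control rate of 14.8% that seems meant for this population but leaves no trace in the result. If the stated 80% does not belong to the test that will be run, a null primary result could be taken as good evidence of no effect when the chance of missing the planned effect was nearer 30% than 20%. It is also unclear which effect the trial was sized to detect.

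**Working it through.** **Inputs.** From S. 3.3.2: 4.9% and 10.7% (ratio 0.107/0.049 = 2.18), control rate 14.8%, power 80%, significance level 5%, retention 80%, total 990. From S. 3.4: p<0.05, logistic regression, missing counted as non-quitter.

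**Formula** (two proportions, equal arms, normal approximation, pooled variance under the null):

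n = [z_a √(2p̄(1−p̄)) + z_b √(p1(1−p1) + p2(1−p2))]² / (p2−p1)²

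z_b = 0.842 for 80% power; z_a = 1.645 one-sided or 1.960 two-sided.

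**1. Reproducing 264.** With p1 = 0.049 and p2 = 0.107: p̄ = 0.078, √(2p̄(1−p̄)) = 0.3793, √(p1(1−p1)+p2(1−p2)) = 0.3770, difference 0.058.
- One-sided: (1.645 × 0.3793 + 0.842 × 0.3770)² / 0.058² = (0.6238 + 0.3173)² / 0.003364 = 263.3, so 264. This is the protocol's figure.
- Attrition: 264 / 0.80 = 330; 3 × 330 = 990. This step also reproduces.

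**2. The same rates, two-sided.** (0.7433 + 0.3173)² / 0.003364 = 334.4, so 335. Other two-sided formulas give 332 (unpooled variance), 324 (arcsine) and 369 (continuity-corrected). None is near 264. Recruiting for 335 would mean 335 / 0.80 = 419 per arm, 1,257 in total.

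**3. Two-sided power at 264 analysed per group.** Power = Φ[(0.058 × √264 − 0.7433) / 0.3770] = Φ(0.528) = 70.1%. Exact enumeration of the uncorrected test gives 71.3%.

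**4. Two-sided power at the number S. 3.4 analyses.** Missing outcomes count as smoking, so all 330 randomised per arm are in the denominator.
- If 4.9% and 10.7% already count losses as smokers: Φ[(0.058 × √330 − 0.7433) / 0.3770] = Φ(0.823) = 79.5%.
- If they apply to the 80% retained, the rates become 0.8 × 4.9% = 3.92% and 0.8 × 10.7% = 8.56%. Power is Φ(0.506) = 69.4%.

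The protocol does not say which applies.

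**5. Using the 14.8% control rate (two-sided).**

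| Intervention rate | Basis | n per group for 80% | Power at 264 |
|---|---|---|---|
| 32.3% | ratio 2.18 (0.148 × 2.18) | 92 | 99.8% |
| 20.6% | same gain of 5.8 points | 679 | 42% |
| 24.5% | solved backwards from 264 | about 264 | 80% |

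One-sided, the first two rows need 72 and 535. An odds ratio of 2.18 (27.5%) needs 162 two-sided or 128 one-sided. None of these uses of 14.8% with a stated effect gives 264; the 24.5% in the last row has no source in the protocol.

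**6. Another route to a similar number.** Pooling both intervention arms against control (2:1, two-sided, 4.9% against 10.7%) needs 261.2, so 262 controls. Power with 264 against 528 is 80.4%.

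**The case against.** Three objections have weight.

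First, the one-sided test is not the only reconstruction. S. 3.3.2 does not name the contrast, and pooling the two intervention arms gives about 262 with a two-sided test. This stands as arithmetic. But no section states pooling, and S. 3.3.7 allocates to three separate arms. So a reader might infer that the investigators must have used a one-sided test; the documents do not establish that. They show only that 264 matches one.

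Second, two-sided testing is an inference. The protocol leaves the sidedness out, so it does not contradict itself in words. This also stands. The inference rests on an unqualified p<0.05 rule, an ordinary logistic regression and the absence of any one-sided declaration. If a one-sided test was intended, it is undeclared and the paragraph needs the same repair.

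Third, 70% is not the trial's power without qualification. Under the missing-as-non-quitter rule 330 per arm are analysed, and on the favourable reading power is 79.5%, in effect the stated 80%. The documents do not settle which reading is right, so a flat claim that the trial has 70% power goes too far.

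It is also tempting to call the 14.8% and the 4.9% contradictory. They are literature rates from different settings, and quoting both is no contradiction. The fault is that the paragraph does not say which one is used. Nor do the inputs all point to too small a trial: with the stated ratio on a 14.8% control rate, power is close to 100%.

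**Conclusion.** The point holds in this limited form. For an arm-to-arm comparison of 4.9% with 10.7%, 264 per group matches 80% power only when the test is one-sided, and the protocol declares no such test. Under the conventional two-sided 5% test the requirement is 335 per group. Power is about 70% with 264 analysed, and between 69% and 79.5% with the 330 per arm that the missing-data rule analyses. The 14.8% control rate does not enter the figure. Depending on whether the ratio or the absolute gain is carried over to it, two-sided power at 264 runs from 99.8% down to 42%, the latter on the assumption that a gain of 5.8 points transfers.

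These results assume the normal approximation, equal arms, individual-level analysis and a separate 5% test for each intervention arm against control. They include no clustering and no allowance for two comparisons; either would raise the required number. The attrition step from 264 to 990 is correct.

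**What to change.** Rewrite the sample size paragraph in S. 3.3.2, keeping N = 990:

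- State one control rate, and say what the other cited rate is for.
- Name the contrast: each intervention arm against control.
- State a two-sided 5% test.
- State the number analysed under the missing-as-non-quitter rule (330 per arm), and whether the cited rates already count losses as smokers.
- Replace the claim that 264 per group give 80% power for 4.9% against 10.7%. The two-sided figures are 335 per group needed, about 70% power with 264 analysed, and 69% to 79.5% with 330 analysed.
- If a detectable rate from a 14.8% control is shown (24.5% at 264 per group), label it a sensitivity figure. It is solved backwards from the sample size and must not be presented as a planning effect.

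The cost is one paragraph of rewording. No participants are added and the analysis does not change. The downside is that the stated power becomes less favourable.

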### **S. 3.3.3. Measurements**

#### *S. 3.3.3.1. Demographics information sheet*

The participants will be collected by using a self-designed demographics information questionnaire which is the same with the one used in the pilot study. The content of the demographics information sheets will include the age, gender, occupation, family income, education level, the number of child, partners' smoking status, medical history, and alcohol using.

#### *S. 3.3.3.2. Smoking characteristics*

The baseline of smoking characteristics will be collected through a structured questionnaire set. The content of the structured questionnaire set will include the, levels of daily cigarette consumption, history of past quit attempts, nicotine dependency assessed by the Fagerstrom Test of Nicotine Dependence.

#### *S.3.3.3.3. The Fagerstrom Test of Nicotine Dependence (FTND)*

The FTND is a standard instrument for assessing the intensity of physical addiction to nicotine, developed by Karl-Olov Fagerström and modified by Todd Heatherton [63, 64]. The test was designed to provide an ordinal measure of nicotine dependence related to cigarette smoking. It contains six items that evaluate the quantity of cigarette consumption, the compulsion to use, and dependence. In scoring the Fagerstrom Test for Nicotine Dependence, yes/no items are scored from 0 to 1 and multiple-choice items are scored from 0 to 3. The items are summed to yield a total score of 0-10. The higher the total Fagerstrom score, the more intense is the patient's physical dependence on nicotine.

#### *S.3.3.3.4. Smoking Self-efficacy Questionnaire (SEQ-12)*

Self-efficacy of participants against tobacco will be assessed by using by the SEQ-12. The SEQ-12 is categorized into two subscales, namely internal stimuli (6 items) and external stimuli (6 items), with total possible scores ranging from 6 to 30 for both internal stimuli and external stimuli. Higher scores of the SEQ-12 on both subscales indicate greater self-efficacy to refrain from smoking.

The psychometric properties of this scale have been empirically examined with the Cronbach's alpha coefficients of 0.95 and 0.94 for internal stimuli and external stimuli, respectively, indicating excellent internal consistency. The intraclass correlation coefficients were 0.95 and 0.93 for internal stimuli and external stimuli, respectively, demonstrating excellent test-retest reliability[2].

#### *S. 3.3.3.5. the Short Form 12 (SF-12) Health Survey*

The short form 12 (SF-12) health survey has been extensively studied and used as a valid measure of health-related quality of life in a variety of population groups, no systematic studies have described the reliability of the measure in patients with behavioral conditions or serious mental illness (SMI).

### **S.3.3.1. Interventions**

#### *S. 3.3.4.1. Smoking hazard videos+brief advice+Pamphlet*

The videos which presented the health effects of smoking, especially emphasizing the importance of smoking cessation on the fetal and pregnancy, will be sent through the smartphone to the participants in the intervention group 1. Also the participants will receive a brief quit advice and pamphlet material related to the smoking cessation at the baseline.

#### *S. 3.3.4.2. Smoking hazard text-messaging+brief advice +Pamphlet*

Text message with the same context with the video will be sent to the participants in the intervention group 2. Also the participants will receive a brief quit advice and pamphlet material related to the smoking cessation at the baseline.

#### *S. 3.3.4.3. Brief advice+Pamphlet*

Participants in the control group will be given a very brief, minimal and general smoking cessation advice during the first assessment. A pamphlet showed the information related to the smoking cessation will be allocated to them at the same time.

#### *S. 3.3.4.5. Follow-up*

All participants will be followed up at one week, one-month, three-month and six-month point by telephone. And the 6-month point is also the end point of the follow up.

### **S. 3.3.5. Validation of quitting**

The level of exhaled carbon monoxide (CO) level will be used as the biomedical marker for assessing the smoking cessation [65].

### **S. 3.3.6. Outcome assessments**

#### *S. 3.3.6.1. Primary outcome*

The primary outcomes are self-reported 7-days point prevalence quit rate at 6-month. Subjects reporting not smoking in the past 7-days at 6-month will be regarded as abstinence from smoking.

#### *S. 3.3.6.2. Secondary outcome*

1. Biomedical validated smoking abstinence: smoking abstinence will be defined as exhaled carbon monoxide (CO) level < 4ppm
2. Smoking reduction: cigarette consumption reduced by at least 50% compared with the

baseline at 6-month.

3. Level of readiness to quit smoking at 6 month

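### Validated abstinence is defined by a CO reading below 4 ppm alone, so a man who reports smoking can be counted as a validated quitter

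*Protocol*

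**What the plan says.** All references are to the protocol.

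- **Primary outcome (S. 3.3.6.1).** Self-report only: "Subjects reporting not smoking in the past 7-days at 6-month will be regarded as abstinence from smoking".
- **First secondary outcome (S. 3.3.6.2).** It is titled "Biomedical validated smoking abstinence", and the rule is "smoking abstinence will be defined as exhaled carbon monoxide (CO) level < 4ppm". Nothing is said about self-report or timing. The next two outcomes in the list, reduction and readiness to quit, are both tied to 6 months.
- **Validation of quitting (S. 3.3.5).** Exhaled CO "will be used as the biomedical marker for assessing the smoking cessation". No rule is given for combining it with what the man reports.
- **Follow-up (S. 3.3.4.5).** "All participants will be followed up at one week, one-month, three-month and six-month point by telephone". The 6-month contact is named as the end of follow-up.
- **Data collection (S. 3.3.7).** "The biochemical validation will be done by a staff member who has not delivered the intervention and conducted the telephone counselling follow-up". The only CO measurement given a time is the first: "exhaled carbon monoxide (CO) level at the baseline will be assessed by the research nurses". The same section says that participants are not blinded.
- **Entry (S. 3.3.2).** Men qualify on "smoking at least one cigarette per day averagely during the past 1 months", with smoking verified by CO. No entry cut-off is stated.
- **Analysis (S. 3.4).** Information missing at follow-up counts as not having quit. The regression of outcomes on intervention is at 6 months.

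**The concern.** Validation means checking a claim. Here the claim is seven days without smoking, and the check should be able to overturn it but never to replace it. The written rule lets the reading stand alone. A man can then fail the primary outcome on his own account and still succeed on the outcome meant to be stricter.

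This matters because the primary outcome is self-reported in an unblinded trial, and CO is the only objective check on it. The population makes low readings among continuing smokers plausible. Entry is open from an average of one cigarette a day, and halving consumption is itself a secondary outcome, so light and reduced smokers are expected at follow-up. The rule rests on a CO level, with no condition covering the seven days of the primary outcome. Smokers misclassified as quitters at a similar rate in all arms would pull the rate ratio towards 1.

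**Working it through.** **Reading the rule**

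The two definitions classify a man at 6 months as follows:

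| He reports, past 7 days | CO reading | Primary outcome | Validated outcome as written | Validated outcome if both are required |
|---|---|---|---|---|
| no smoking | below 4 ppm | abstinent | abstinent | abstinent |
| no smoking | 4 ppm or more | abstinent | not abstinent | not abstinent |
| smoking | below 4 ppm | not abstinent | **abstinent** | not abstinent |
| smoking | 4 ppm or more | not abstinent | not abstinent | not abstinent |

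Only the third row differs between the last two columns. No sentence in S. 3.3.5, S. 3.3.6, S. 3.3.7 or S. 3.4 removes that man from the count. Because the third row can add men, the validated rate is not bounded above by the self-reported rate.

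**Illustration of size**

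Inputs from S. 3.3.2: planning quit rates of 10.7% (intervention) and 4.9% (control). The stated ratio reproduces: 0.107 / 0.049 = 2.18.

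Assumptions that are not in the documents:

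- a share f of continuing smokers reads below 4 ppm, the same in each arm;
- every continuing smoker is tested;
- the planning rates are the true quit rates, and every true quitter reads below 4 ppm.

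Observed validated rate = q + f(1 − q), where q is the true quit rate.

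| f | Intervention: 0.107 + 0.893f | Control: 0.049 + 0.951f | Ratio | Difference |
|---|---|---|---|---|
| 0 | 0.1070 | 0.0490 | 2.18 | 5.8 points |
| 5% | 0.1517 | 0.0966 | 1.57 | 5.5 points |
| 10% | 0.1963 | 0.1441 | 1.36 | 5.2 points |
| 20% | 0.2856 | 0.2392 | 1.19 | 4.6 points |

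The difference shrinks only by the factor (1 − f). The ratio falls faster because the control rate is low. At f = 5% the validated control rate would be 9.7%, against a true rate of 4.9%.

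**Sensitivity to who is tested**

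Now suppose only 80% of each arm is tested (the retention assumed in S. 3.3.2), all true quitters are among them, and untested men count as non-quitters. The observed rate is q + f(0.80 − q), that is 0.107 + 0.693f and 0.049 + 0.751f. The ratios are:

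- f = 5%: 0.1417 / 0.0866 = 1.64
- f = 10%: 0.1763 / 0.1241 = 1.42
- f = 20%: 0.2456 / 0.1992 = 1.23

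If only men who report quitting are tested, the third row of the first table is empty and this dilution is zero.

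**The case against.** **The intent is fairly clear.** The outcome is titled as validated abstinence, a section on validating quitting precedes it, and it follows directly after a self-report definition. A sensible team would probably apply CO to claimed quitters. This stands as a reading of intent, but no sentence states that both conditions must hold, and the protocol fixes the definition without them.

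**The timing is implied.** S. 3.3.4.5 ends follow-up at 6 months and S. 3.4 analyses outcomes there. This largely stands. The omission should be repaired, but no other time point is suggested.

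**Entry smoking is CO-verified.** This should limit how many men read low at baseline and bears directly on f. It stands, with two limits: no entry cut-off is given, and men may cut down after entry without quitting.

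**The numbers are hypothetical.** This stands. The documents give no figure for f and do not say who is tested.

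**A stronger reading.** From S. 3.3.4.5 a reader might infer that a follow-up conducted by telephone can never yield a CO reading, so that under the missing-data rule every man would become a non-quitter. The documents do not support this. S. 3.3.7 assigns biochemical validation to a staff member separate from the telephone follow-up, so a further contact is implied. S. 3.3.7 also refers to Figure 2 for the detailed procedure. That figure is not reproduced in the text available and may give the logistics. What remains is that the two sections need to be reconciled.

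**Conclusion.** The point holds as a defect in a stated outcome definition. Read literally, the rule counts an admitted smoker with a reading below 4 ppm as a validated quitter. The outcome therefore does not do what its title promises, and its rate could exceed the self-reported rate. This conclusion rests on the wording alone and needs no numerical assumption.

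The size is unknown. The fall in the ratio from 2.18 to between 1.57 and 1.19 holds only if 5% to 20% of continuing smokers read low, equally in each arm, and all are tested. It would be smaller with incomplete testing and nil if only claimed quitters are tested. It should not be cited as an expected effect.

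The primary outcome, its analysis and the sample size are untouched. For a secondary outcome that is the only objective check in an unblinded trial, the correction should be made.

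**What to change.** 1. In S. 3.3.6.2, define validated abstinence as both self-reported no smoking in the past 7 days at 6 months **and** exhaled CO below 4 ppm. The protocol's own cut-off is kept.
2. State that men who report smoking count as not abstinent whatever their reading, and that men who report quitting but are not tested also count as not abstinent. The second part already follows from the missing-data rule in S. 3.4.
3. Reconcile S. 3.3.4.5 with S. 3.3.7 by stating when the planned CO test takes place relative to the 6-month call, and who is tested. Under the combined definition only men who report quitting need a test.

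Cost: the definition changes in wording only and adds no new measurement. Testing only claimed quitters needs fewer readings than testing everyone, but the timing of the test has to be set and kept to. The statistical price is that true quitters who are not tested count as smokers, so the validated rate will be lower than the true one. Reporting the number of claimed quitters tested in each arm would let readers judge this.
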